### Compliance

The ability of the patient to perform exercises at home is documented at the beginning of all physiotherapy sessions and if not, the reason is asked.

## Discussion

### Why publish a study protocol

It is decided to publish the study protocol before obtaining results as we think it is important to share our thoughts and decisions about designing this study with other researchers in the field. Furthermore, a research article offers only a limited space to explain and reflect on the methods of a trial. Finally, researchers in the field are aware of which study is ongoing, which prevents wasteful duplication of research effort.

### Bias and confounding

To minimize information bias, the performance of physiotherapists experienced in women's health is standardized. First, only physiotherapists registered at the NVFB are able to participate in this study. Registration approval indicates satisfying the outlined quality criteria by the NVFB. Second, participating physiotherapists receive a general and physiotherapy protocol of the PhysioFIT-study composed by experts in the field. Third, participating physiotherapists attend a general meeting. An individual visit is organised when a patient is referred to a non-attending physiotherapist. During the meeting, the physiotherapists were instructed on the general and physiotherapy protocol, a DVD-film illustrated the intended rectal balloon training and questions and discussions were raised. Some small adaptations were made in the protocol based on remarks from the physiotherapists.

To further minimize information bias, adaptations were made to the rectal balloons of the supplier. The current balloon reached the sigmoid colon, as soon as the balloon was filled with approximately 180 ml, possibly resulting in colic pains. This prevented the measurement of a higher maximal tolerated volume, although 180 ml is rarely reached. As this balloon was inadequate for this trial, adapted rectal therapy balloons were developed in cooperation with the supplier.

In this trial, it is impossible to blind on all levels. Most importantly, the measurement of the primary outcome is blinded as well as the outcome assessors. Blinded double data-entry is performed to assure correct data-entry.

Confounders that are taken into account are presence of urinary incontinence, use of anal tampons, patients' compliance and medication use. The presence of urinary incontinence can influence the perception of patients' quality of life and estimation of severity of FI, thereby distorting the scores on the FIQL, PREFAB and GPE-scores. Furthermore, patients' compliance to the home exercise program determines therapy intensity and indirectly therapy success. Therefore, the physiotherapist asks each session patients' compliance to the home exercise program as formulated. The patient gives an explanation in case of insufficient compliance. Finally, the use of anal tampons and medication use can influence the number of involuntary events and stool consistency, as measured during the visits to the physician and in the diary.

### Trial arms and patient selection

The effectiveness of rectal balloon training is assessed in a randomized controlled trial using two trial arms. A third trial arm with RBT as a single treatment option is not included, for the following reasons:

RBT, as a solitary therapy option, has another suggested goal than PFMT. PFMT is hypothesized to improve strength, coordination and endurance. RBT is hypothesized to teach patients with an insensitive rectum to discriminate and respond to smaller rectal volumes of distension until a normal level of sensory threshold is reached. Patients with a hypersensitive rectum are taught to tolerate larger volumes by the use of progressive distension and urge resistance until a normal level of urge sensation is reached. In our first trial arm RBT is performed to strengthen the effect of PFMT. To compare this trial arm with only PFMT, the additional effect of RBT can be assessed.

In addition, a review by Siv Mørkved, based on seven randomized controlled trials published between 1999 and 2005 on conservative treatment (PFMT with or without biofeedback and electrical stimulation) concluded that PFMT with and without biofeedback seems to be effective in reducing FI [35]. This shows us that many physiotherapy intervention trials are designed with PFMT being at least part of the intervention. Adding a trial arm enables us to assess the effect of a more optimized physiotherapy intervention. Based on this and consensus in patients with moderate to severe FI, it is decided that PFMT alone should be at least the minimum standard of care in this disabled patient group.

Finally, as a result of strict in- and exclusion criteria we expect to include only one patient a week, resulting in an unacceptable long inclusion and follow-up period or insufficient power when extending to three trial arms.

### Secondary goals

Secondary goals of the PhysioFIT-study are to assess the psychometric properties of the PREFAB-score in clinical practice. In addition, baseline measurements are checked for their ability to predict outcome of physiotherapy.

Furthermore, the responsiveness of the Vaizey score is reviewed. The Vaizey score is a more common used severity score in surgical trials. But less is known about the responsiveness of the Vaizey score in physiotherapy trials. One study with comparable in- and exclusion criteria and study population made a first attempt to correlate the Vaizey score with a Global perceived effect score (31). Patients with a decrease of 9 points rated their situation "much better" than before physiotherapy treatment, patients with a decrease of 4 points rated their situation "better" and the group that rated their situation "(much) worse or equal" had a decrease in 1 point (patients were asked in a standardized interview to score their current situation on a scale of 1 (much worse), 2 (worse), 3 (no change), 4 (better), or 5 (much better)). We decided that rating the patients' situation as "better" is a minimally important change (MIC), expressed in an absolute number and not in a certain percentage.

Next to the Vaizey score we included the subjective GPE score (range 1–9) in our trial as an additional outcome measure, as we believe it is important to further investigate the responsiveness of the Vaizey score in patients with FI in physiotherapy trials.

Finally, it is expected that the outcome after physiotherapy interventions is dependent on the baseline Vaizey score; therefore we will perform a stratified analysis on baseline severity scores and change scores.

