### Recruitment, informed consent and randomization

The medical ethics committee of the University Hospital Maastricht/Maastricht University approved the PhysioFIT-study. The physician points out during the first visit that the patient is eligible to participate in the trial. The patient is provided with patient information sheets and information on the diagnostic tests. Participating patients sign informed consent at the beginning of the second visit, allowing eligible participants two months to decide to participate.

An independent research assistant performed the blocked randomization (size of four). A computer-generated randomization list is prepared in advance. The independent research assistant contacts the physiotherapist by telephone to inform about the referral and the allocated treatment.

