▪ PREFAB-score: the PREFAB-score is a modified version of the widely used and accepted PRAFAB-score in the urinary incontinence field. The PRAFAB-score is a simple and quickly obtained score which summarizes several objective and subjective components of the severity of urinary incontinence complaints (ranging from 5–20) [33]. The score has proven to be reliable, valid and responsive [34]. Since most of the PRAFAB-score, except for the "amount" item, is applicable to fecally incontinent patients as well, it is suggested to adapt the PRAFAB-score to fecally incontinent patients. From the patients' point of view, two aspects about excretion of feces are reported to be highly embarrassing and affecting social life and body image: whether the excretion can be held up by a pad or not and whether excretion can be smelled by the environment or not. These two aspects, reflecting social limitations, are therefore integrated in the modified PRAFAB-score (min-max = 6–20; range = 15).

▪ Global perceived effect (GPE) (Table 2): this subjective score reflects the change in complaints after physiotherapy treatment compared to the period before treatment and ranges from 1–9 points. A score of 8 or 9 indicates much worsening of complaints and is an indication to consider co-interventions.

**Table 2 T2:** Global perceived effect (GPE-score)

To which degree have your complaints changed compared to the period before physiotherapy treatment?
At the moment, the complaints are .....
1. Very much improved
2. Much improved
3. Moderately improved
4. Slightly improved
5. Unchanged
6. Slightly worse
7. Moderately worse
8. Much worse
9. Very much worse
..... compared to the period before physiotherapy treatment

Follow-up measurements are scheduled at 3, 6 and 12 months after inclusion. Primary outcome measure is the Vaizey score [28]. Success after physiotherapy is defined as a reduction in Vaizey score of more than four points (16.7%) compared to baseline measurement. Recently, it is reported that patients who rated their situation to be better, improved four points on the Vaizey score [31]. Secondary outcome measures are anorectal resting and squeeze pressure, rectal capacity, anorectal sensation, diary results, FIQL, PREFAB-score and GPE-score.

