### Sample size

The sample size is calculated based on data from a recently published cohort study on pelvic floor rehabilitation in fecally incontinent patients [31]. Patients who reported their situation to be better after pelvic floor rehabilitation showed a mean improvement score of 4.33 points on the Vaizey score and patients who rated their situation to be equal or (much) worse showed a mean improvement score of one point (baseline average Vaizey score is 18). As subjective improvement can not be projected as decimals on the Vaizey score, we calculated two sample sizes: (1) with exact scores and (2) with absolute scores to correspond with the Vaizey score and estimate of the minimally important change (MIC). The absolute difference in improvement of four points between the patients who rated themselves to be better and the patients who rated themselves to be equal or (much) worse is considered the MIC on the Vaizey score between both trial arms [31].

The first sample size is calculated using an average Vaizey score of 13.67 and a standard deviation of 8.45 for sample 1 and an average Vaizey score of 17 and a standard deviation of 3.90 for sample 2, which resulted in a sample size of 106 patients. The second sample size is calculated using an average Vaizey score of 13 and a standard deviation of 8.45 for sample 1 and an average Vaizey score of 17 and a standard deviation of 3.90 for sample 2, which resulted in a sample size of 73 patients. The sample size is in a range of 73 to 106 patients and we decided to include at least 106 patients to feel confident about the required sample size.

All calculations assume a one-sided effect (first trial arm has a better outcome than second trial arm), an alpha of 0.05, a power of 80% and an expected drop-out of 10%. It is expected that the drop-out will be minimal since patients will be greatly motivated to participate and adhere to the protocol, by experiencing such an embarrassing and socially restricting disorder.

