### Data analysis

In case of longitudinal missing data, imputation is performed with the last observation carried forward method. Main outcome is tested according to the intention to treat principle. Both treatment groups are checked for comparability regarding baseline data. An independent t-test is done for continuous variables and a Chi-square test for categorical variables. Analyses are performed to compare differences within groups between baseline and short-term follow-up (3 months) and long term follow-up (6 and 12 months) regarding primary and secondary outcome measures. A subgroup analysis is done for the patients with and without co-interventions. Analysis of variance is used to determine the difference in mean change of outcome measure between clinical subgroups. A two-tailed p-value of 0.05 is considered to indicate statistical significance. Data analysis is done using SPSS version 13.0 (SPSS, Inc., Chicago, Illinois). Confounders that are taken into account are presence of urinary incontinence, use of anal tampons, compliance and medication use.

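### Baseline Vaizey score is expected to drive outcome but is not in the covariate list, and the stratified analysis offered in its place names change scores as if they were a stratifying variable

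*Protocol article*

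**What the plan says.** - **Expectation.** The Discussion (Secondary goals) states that "it is expected that the outcome after physiotherapy interventions is dependent on the baseline Vaizey score".
- **Response.** The same sentence continues: "therefore we will perform a stratified analysis on baseline severity scores and change scores". The strata, their cut-points and the role of the change scores are not defined.
- **Covariates.** Data analysis says: "Confounders that are taken into account are presence of urinary incontinence, use of anal tampons, compliance and medication use". Bias and confounding, in the Discussion, repeats this list. Baseline Vaizey is in neither place.
- **Analysis of change.** Data analysis says: "Analysis of variance is used to determine the difference in mean change of outcome measure between clinical subgroups". No baseline covariate is mentioned.
- **Randomisation.** "An independent research assistant performed the blocked randomization (size of four"); no stratification by severity is stated.
- **Outcome.** "Primary outcome measure is the Vaizey score", and the score is among the baseline measurements, so the covariate is available at no extra effort.

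**The concern.** The authors name one variable as a driver of outcome, measure it at baseline, and then leave it out of the variables they will account for. Two things are at stake.

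1. **Precision and chance imbalance.** Randomisation is not stated to balance severity, so the arms may differ at baseline by chance. An unadjusted comparison of change or of follow-up scores carries that imbalance into the estimate. It also leaves unused whatever the baseline explains of the follow-up score.
2. **Conditioning on the outcome.** Change in Vaizey is the outcome itself, measured after randomisation. If arms were compared within strata of change, most of the treatment effect would be absorbed by the strata.

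**Working it through.** **Inputs from the protocol (Sample size).** "average Vaizey score of 13.67 and a standard deviation of 8.45 for sample 1"; "average Vaizey score of 17 and a standard deviation of 3.90 for sample 2, which resulted in a sample size of 106 patients". The difference is 17 − 13.67 = 3.33. The calculation is one-sided, alpha 0.05, 80% power, 10% drop-out. Data analysis uses a two-tailed 0.05.

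**Inputs assumed.** The baseline/follow-up correlation ρ is not given; 0.3 to 0.7 is used. The baseline SD is not given either; two cases are shown.

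**Step 1. Reproduce the stated size.** Sum of variances: 8.45² + 3.90² = 86.61, so the pooled SD is √(86.61/2) = 6.58. Per arm: 86.61 × (1.645 + 0.842)² / 3.33² = 48.29. Total 96.6; × 1.1 = 106.2, against 106 stated. The calculation uses follow-up scores and takes no credit for baseline.

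**Step 2. Variance per patient under each analysis.** With baseline SD s_b and follow-up SD s_y:
- change score: s_b² + s_y² − 2ρ·s_b·s_y
- ANCOVA: s_y²(1 − ρ²)

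If s_b = s_y, the ratio ANCOVA/change reduces to (1 + ρ)/2. With s_y = 6.58:

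| ρ | ANCOVA variance | Change variance and ratio, s_b = 6.58 | s_b = 4 | s_b = 3 |
|---|---|---|---|---|
| 0.3 | 39.4 | 60.6; 0.65 | 43.5; 0.91 | 40.5; 0.97 |
| 0.5 | 32.5 | 43.3; 0.75 | 33.0; 0.98 | 32.6; 1.00 |
| 0.7 | 22.1 | 26.0; 0.85 | 22.5; 0.98 | 24.7; 0.89 |

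The smaller baseline SDs are the more plausible. Entry requires a score of at least 12 on a scale that ends at 24, so the baseline SD can hardly exceed 6 and is probably well below it.

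Against an unadjusted comparison of follow-up scores, the ratio is 1 − ρ², that is 0.91, 0.75 and 0.51, whatever the baseline SD.

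**Step 3. Power in the equal-SD case.** Evaluable per arm: 106 × 0.9 / 2 = 47.7. Two-sided 0.05, difference 3.33, normal approximation: Φ(3.33 / (SD·√(2/47.7)) − 1.96). Unadjusted follow-up scores give about 70%. Change score against ANCOVA gives 55% and 74% (ρ = 0.3), 70% and 81% (0.5), 89% and 93% (0.7). This is the favourable case for ANCOVA over change scores.

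**Step 4. Stratifying on baseline, and on change.** Simulation with 48 per arm, 3000 runs, normal scores and equal SDs of 6.58. The change strata were cut at a reduction of at least 4 points.

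| Two-sided power | ρ = 0.3 | ρ = 0.5 | ρ = 0.7 |
|---|---|---|---|
| Unadjusted change | 55% | 70% | 88% |
| Two baseline strata | 65% | 76% | 91% |
| Four baseline strata | 69% | 79% | 91% |
| ANCOVA | 73% | 81% | 92% |
| Strata of change | 21% | 30% | 46% |
| Mean estimate, strata of change (true −3.33) | −1.21 | −1.26 | −1.28 |

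Baseline strata gave estimates of about −3.33 and type I error of about 5%. Strata of change gave type I error of about 4 to 5%, so the damage is attenuation, not false positives.

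**The case against.** The sentence on stratification closes a section on secondary goals, straight after paragraphs on the responsiveness of the Vaizey score. It names no comparison between arms and does not say that it replaces the primary comparison. It may well mean that change is analysed within strata of baseline severity, which is valid. Stratifying on baseline is itself a form of baseline adjustment. The analysis of variance in Data analysis refers to clinical subgroups and does not fix an unadjusted test between arms. An article may also leave the primary model to a fuller document.

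Much of this stands. A reader might infer that the plan loses validity, that stratifying throws away most of the precision a covariate would give, or that the trial misses a two-sided power it promised. The documents support none of these. Baseline strata are unbiased and recover more than half of the gain in each simulated case. The literal reading of the change-score wording is only one of two. The only power stated is 80% for a one-sided effect; its conflict with the two-tailed test is a separate matter.

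What remains does not rest on silence. The article gives a named list of covariates, twice, and omits the one variable it expects to matter. The reference to change scores is open to a reading that would harm the estimate.

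**Conclusion.** The point holds as an inconsistency between the stated expectation and the stated covariates, together with one ambiguous sentence.

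- **Omission.** No baseline-adjusted comparison between arms is stated for the primary outcome. In large samples ANCOVA is never less precise than the change-score or the unadjusted follow-up comparison, so adding the covariate is a safe improvement.
- **Size of the gain: uncertain.** For ρ of 0.3 to 0.7, the variance falls to 0.65 to 0.85 of the change-score variance with equal SDs, but only to 0.89 to 1.00 with a baseline SD of 3 to 4 against 6.58. Over change scores the gain could therefore be negligible. Over unadjusted follow-up scores it depends on ρ alone.
- **Stratifying on baseline.** Valid, at a cost of about 1 to 9 power points against ANCOVA under the simulated assumptions.
- **Stratifying on change.** Only if read literally and applied to the comparison between arms: the estimate falls to somewhat over a third of its true size (1.21/3.33 = 0.36 to 1.28/3.33 = 0.38).

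**What to change.** 1. State that follow-up Vaizey is compared between arms by ANCOVA with baseline Vaizey as a continuous covariate.
2. Treat each continuous secondary outcome that is measured at baseline in the same way, with its own baseline value. The global perceived effect score has no baseline and is outside this rule.
3. Examine whether the effect of balloon training varies with severity by one arm-by-baseline-Vaizey interaction, labelled secondary.
4. Delete change scores as a stratifying variable, or reword the sentence so that change is analysed within baseline strata.

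The cost is analysis wording only. Baseline Vaizey is already collected, and no further patients, visits or measurements are needed.

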### Transfer of knowledge and implementation

The results of this trial will be used for recommendations in the guideline of physiotherapy in fecally incontinent patients. This guideline will be developed according to method of clinical practice guideline development of the Royal Dutch Society for Physical Therapy (KNGF) [36].

### Spin off

Often, a trial is designed with the objective to make a difference in clinical daily practice. This section elaborates on what we believe might influence clinical practice.

Based on the results of this trial, baseline measurements are checked for their ability to be a prognostic factor for a good or poor outcome after physiotherapy. In this way, patients can be selected who benefit most of the proposed physiotherapy intervention. Furthermore, this trial can give information on the number of physiotherapy sessions after which more sessions are of no further benefit. Continuation or ending of therapy will have the same outcome at that point. Finally, if the effectiveness of a certain physiotherapy intervention is established, physicians can make a well-founded decision for referral to physiotherapy treatment, in stead of proceeding with surgical treatment. In conclusion, this trial might add to clearer referral patterns and better cooperation between physicians and physiotherapists.

In case of insufficient result of physiotherapy and proceeding to surgical treatment, the received physiotherapy intervention can still be of value. Patients already learned to be aware of their pelvic floor muscles and know how to contract them in an environment without post-surgical stress. Besides, their pelvic floor is probably in a better condition. Future research in this area can focus on the effect of different pre-operative physiotherapy interventions on the success of surgery in FI.
